**f. Outcomes at age 11 years (PROBIT III)**

***Table 4: Intra-class correlation coefficients (ICC) for measurements taken in PROBIT III***

| *Measurement* | *ICC* |
| --- | --- |
| Standing height | 0.03 |
| Sitting height | 0.03 |
| Weight | 0.02 |
| Bioimpedance | 0.01 |
| Mid-upper arm circumference | 0.03 |
| Systolic blood pressure | 0.12 |
| Waist circumference | 0.07 |
| Hip circumference | 0.03 |
| Head circumference | 0.10 |
| Triceps skinfold thickness | 0.12 |
| Subscapular skinfold thickness | 0.04 |
| Glucose | 0.08 |

At 11.5 years (PROBIT III), we investigated effects of breastfeeding on growth and cardio-metabolic risk factors. Pediatricians performed anthropometric measurements on mothers and children, and collected fasting blood via fingerstick. We have completed all study visits and await final data entry and results of laboratory assays. The participation rate - 13,891 children were seen – attests to our ability to maintain excellent follow-up and thus minimize retention bias. Intra-class correlation coefficients were extremely low for all measured outcomes (**Table 4**), indicating valid measurements with a low degree of clustering.

In an interim intention-to-treat analysis (n = 12,374), cluster-adjusted mean differences in experimental vs. control groups were essentially null: 0.16kg/m^2^ (95% CI: -0.08, 0.40) for BMI; 0.43% (-0.15, 1.01) for body fat; 0.33cm (-1.25, 1.92) for waist circumference; 0.11mm (-1.53, 1.74) for triceps skinfold thickness; 0.62cm (-0.40, 1.64) for height; and 1.12mmHg (-1.06, 3.30) for systolic blood pressure.^141^ The odds ratio for obesity (experimental vs. control arms) was 1.19 (0.95, 1.50). We found similar null results for maternal postpartum adiposity.^142^ We now have a number of papers in progress presenting results of the intention-to-treat analysis of the anthropometric and biochemical study outcomes. Our joint experience leading PROBIT III yields several important messages: we have demonstrated our successful collaboration in leading a PROBIT outcome visit; we achieved high rates of follow-up with little evidence for bias in follow-up or clustering in outcome assessments; and we require 4 years of funding to allow for complete data collection and analysis.

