**2.3.6. Power**

Based on follow-up in PROBIT I-III, we expect 14,000 participants in PROBIT IV. We calculated detectable differences based on this number of subjects in 31 clusters, an intention-to-treat (ITT) analysis, 80% power, 5% significance, and used a realistic value (0.01) of the intra-cluster correlation coefficient (ICC) based on the ICCs of outcomes in PROBIT I-III. The effective sample size in PROBIT IV, allowing for the clustered design, is the total number of anticipated participants (14,000) divided by the design effect (*Deff*), where *Deff* = 1+(*n*-1)×ICC and *n* is the average number of individuals per cluster (n=14,000/31=451).^156^ Thus, the design effect for an ICC of 0.01 is 1+4.5=5.5 and the effective sample size is 2,500 children (14,000/5.5). Expected means and SDs for each outcome were taken from childhood cohorts of similar age. Mean detectable differences, assuming exposure groups are dichotomized at the midpoint, are calculated as the product of the SD of each variable and the standardized difference (i.e. 0.1 given an effective sample size of 2,500^157^). For the categorical atopic eczema outcome at the 16-year follow-up (flexural eczema on skin examination), the study has 94% power at the 5% significance level to detect a 50% reduction in atopic eczema prevalence between the two study groups, similar to PROBIT I.^21^

**Table 5** shows the mean differences that can be detected in the comparison of the two randomized arms by ITT and the corresponding effect due to breastfeeding that would have to be present to achieve those ITT differences. The breastfeeding effect is based on the difference in exclusive breastfeeding at 3 months of 43% in the intervention arm and 6% among controls, and is derived by dividing the ITT differences by 0.37=37% (the difference in exclusive breastfeeding in the 2 arms). For comparison, published differences are shown. The sample size is adequate for detecting important differences in the outcomes (**Table 5**). If we fail to find associations in the ITT analysis, the study is powered to have narrow confidence intervals (CIs) around null estimates. The 95% CIs for zero mean differences, assuming an effective sample size of 1250 in each arm ((14,000/Deff) ÷ 2) and means/SDs in Table 2, would be: cognitive score ± 1.2; FEV_1_ ± 40mls; FVC: ± 45mls; PEFR: ± 60mls/s.

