***Table 5:* *Expected control group means, SDs, and differences detectable (alpha= 0.05, 80% Power)***

| **Continuous Outcomes** | **Mean** | **SD** | **Mean detectable differences: ITT** | **Breastfeeding effect to produce detectable effect** | **Differences observed in other studies** |
| --- | --- | --- | --- | --- | --- |
| Global cognitive score | 100 | 15 | 1.5 | 4.1 | 2-5^16^ |
| FEV_1_ (mls)^a^ | 3345 | 480 | 48 | 130 | 40^59^ |
| FVC (mls)^a^ | 3700 | 575 | 58 | 150 | 54-103^58,59^ |
| PEFR (mls/s)^a^ | 6200 | 800 | 80 | 200 | 180^4,59^ |
| LogMar visual acuity | 0.02^b^ | 0.2^b^ | 0.02 | 0.05 | 0.05^5-7,101,158^ |
| Systolic blood pressure (mmHg)^159^ | 99.9 | 9.6 | 1.15 | 3.11 | Meta-analysis: 1.4 Max difference: 6.5^160^ |
| Diastolic blood pressure (mmHg)^159^ | 57.0 | 6.8 | 0.82 | 2.22 | Meta-analysis: 0.5; Max differences: 3.4^161,162^ |
| Body mass index (kg/m^2^) ^c^ | 16.2 | 2.0 | 0.024 | 0.06 | 0.4^163^; 0.28-0.57^72,164^ |

^a^Data from ALSPAC, standardized for height; ^b^Northern Ireland Childhood Errors of Refraction study (personal communication); ^c^Estimates of means and SDs obtained from ALSPAC.

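### Table 5's BMI SD of 2.0 and the planning ICC of 0.01 together contradict the trial's own 11.5-year precision; the detectable BMI difference is about 0.34 kg/m², not 0.024 or 0.20–0.24

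*Protocol*

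**What the plan says.** Section 2.3.6 (Power) plans for 14,000 children in 31 clusters, with 80% power and 5% significance. For clustering it "used a realistic value (0.01) of the intra-cluster correlation coefficient (ICC) based on the ICCs of outcomes in PROBIT I-III". It concludes that "the design effect for an ICC of 0.01 is 1+4.5=5.5 and the effective sample size is 2,500 children (14,000/5.5"), and it takes a detectable difference of 0.1 SD from that effective size.

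The source of the means and SDs is given separately: "Expected means and SDs for each outcome were taken from childhood cohorts of similar age". The BMI row of Table 5 starts "Body mass index (kg/m^2^) ^c^ | 16.2 | 2.0". It continues with an ITT detectable difference of 0.024, a breastfeeding effect of 0.06, and published differences of 0.4 and 0.28–0.57. A footnote names ALSPAC as the source of the BMI mean and SD, without an age. Section 2.3.6 obtains the breastfeeding effect by dividing the ITT difference by 0.37, and states that the sample size is adequate for important differences in the outcomes.

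Section 2.3.3.f reports the trial's own cluster-adjusted interim result at 11.5 years in 12,374 children: "0.16kg/m^2^ (95% CI: -0.08, 0.40) for BMI". Table 4 in that section lists PROBIT III ICCs from 0.01 to 0.12. Weight has 0.02, and there is no BMI row.

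**The concern.** The protocol holds an observed precision for BMI from the same cohort. A planning SD and ICC should roughly reproduce the confidence interval already obtained, and for BMI they do not.

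The printed 0.024 is only 0.012 SD, so it does not follow from the protocol's own rule and looks like a misplaced decimal. The risk is that someone corrects the decimal to 0.20 or 0.24 and takes the row to be sound, although the inputs behind it are still too favourable. BMI is a named outcome under the adiposity aim, and Table 5 is the basis of the claim that the sample size is adequate for it.

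**Working it through.** **Inputs.** From section 2.3.6: N = 14,000, 31 clusters, ICC 0.01, 80% power, 5% significance (taken as two-sided), contrast 0.37. From Table 5: BMI SD 2.0. From section 2.3.3.f: n = 12,374 and a BMI interval of −0.08 to 0.40. Equal arms, equal cluster sizes and all 31 clusters at 11.5 years are assumed.

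**Formulas.** Deff = 1 + (m − 1) × ICC, with m children per cluster. SE of the difference = 2 × SD × √(Deff/N). Detectable difference = (1.96 + 0.84) × SE = 2.80 × SE.

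**1. The plan's own figures.** m = 14,000/31 = 451.6; Deff = 5.51; effective N = 14,000/5.51 = 2,543. This reproduces the stated 5.5 and 2,500. The standardized difference is 2.80 × 2/√2,500 = 0.112, which the protocol rounds to 0.1. For BMI with SD 2.0:
- 0.1 SD rule: 0.20
- exact formula: 0.22
- multiplier of 0.12 implied by the two blood pressure rows (1.15/9.6 and 0.82/6.8): 0.24

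None gives 0.024, which fits a tenfold slip from 0.24. The adjoining 0.06 carries the slip on (0.024/0.37 = 0.065).

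**2. What SD 2.0 and ICC 0.01 predict at 11.5 years.** m = 12,374/31 = 399; Deff = 4.98; SE = 2 × 2.0 × √(4.98/12,374) = 0.080; half-width = 1.96 × 0.080 = 0.157.

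**3. What was observed.** Half-width = 0.48/2 = 0.24; SE = 0.24/1.96 = 0.122 (0.117 if the interval used t on 29 df). The ratio to the prediction is 1.53 (1.46), so the variance is 2.33 (2.14) times as large. Treating the interim variance as estimated on 29 df, the 95% range of that ratio is about 1.5–4.2 (1.4–3.9 with t). It excludes 1.

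**4. Combinations that reproduce ±0.24** (normal reference):

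| ICC | SD needed |
| --- | --- |
| 0.01 | 3.05 |
| 0.02 | 2.27 |
| 0.027 | 2.0 |

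The interval fixes only SD² × Deff, so it cannot choose between them.

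**5. Check of the method.** For systolic blood pressure, Table 5's SD of 9.6 with Table 4's ICC of 0.12 gives Deff = 48.8 and a predicted half-width of 1.96 × 2 × 9.6 × √(48.8/12,374) = 2.36. The reported interval (−1.06 to 3.30) has 2.18. The formula comes close when the trial's own ICC is used.

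**6. Detectable difference at 14,000 children.** The combinations in step 4 all give about 0.34; for example, SD 3.05 with ICC 0.01 gives 2.80 × 2 × 3.05 × √(5.51/14,000) = 0.34. The choice of z or t moves this only between about 0.32 and 0.36. Allowing for an SE estimated on 29 df gives roughly 0.27–0.46. At the 11.5-year SE, power is about 37% for a true difference of 0.20 and 50% for 0.24.

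**7. Breastfeeding scale.** 0.34 (unrounded 0.343)/0.37 = 0.93. The range runs from 0.27/0.37 = 0.73 to 0.46/0.37 = 1.24. The decimal-corrected figures give 0.20/0.37 = 0.54 and 0.24/0.37 = 0.65.

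**The case against.** The strongest objection is that SD 2.0 may be sound. With Table 4's weight ICC of 0.02, Deff at 11.5 years is 8.96 and the predicted half-width is 0.211 (0.220 with t on 29 df). Against the observed 0.24 the t-based variance ratio is then about 1.19, well inside the sampling range of about 0.55–1.58 for a variance on 29 df. This stands, and it limits the point: the SD is not shown to be wrong. It does not rescue the pair, because it concedes that 0.01 is too low for BMI. SD 2.0 with ICC 0.02 at 14,000 children already gives a detectable difference of 0.30.

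Unequal cluster sizes could also widen the interval. On the usual formula, however, they would need a coefficient of variation of about 1.2–1.3 to explain the gap. The same clusters are followed in PROBIT IV, so the detectable difference would still be about 0.34.

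Some stronger readings are tempting but not supported:
- A reader might infer that the mean of 16.2 comes from a cohort too young for this follow-up. The mean does not enter the width of an interval, the footnote gives no age, and the protocol gives no BMI means by age.
- A reader might infer that the similar-age statement is refuted. It covers only means and SDs; the ICC is attributed to PROBIT I–III, and the ICC alone may account for the gap.
- A reader might set the published 0.28 directly against the ITT figure of 0.34. The protocol compares published differences on the breastfeeding scale, after division by 0.37.

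Finally, BMI does not set the sample size, the cohort is fixed, and the protocol's statement on intervals around null estimates omits BMI. These points limit the consequence to a table row and a claim of adequacy.

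**Conclusion.** The point holds for the pair of inputs. SD 2.0 and ICC 0.01 predict ±0.16 kg/m² where the trial found ±0.24, a gap beyond sampling error. At least one is too low; the documents do not settle which, though they point at least partly to the ICC.

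The best-supported ITT detectable difference is about 0.34 kg/m², roughly 0.27–0.46. This assumes that the 11.5-year precision carries over to age 15–16, with equal arms and equal cluster sizes, and it rests on one SE from 31 clusters.

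The breastfeeding effect needed, about 0.93 kg/m², exceeds every published difference in the row, and so does the lower end of its range (0.73). The adequacy statement is therefore unsupported for BMI. Not all of the shortfall comes from this defect: with the decimal corrected and the inputs left alone, 0.54–0.65 already exceeds 0.28 and 0.4.

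**What to change.** Recompute the BMI row of Table 5, both the ITT detectable difference and the breastfeeding effect, with the BMI SD and ICC observed in the PROBIT III children, and report those two values beside it. Qualify the adequacy statement in section 2.3.6 so that it does not extend to BMI at the published effect sizes.

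The cost is a short recalculation from data the investigators already hold. The sample size, the analysis and the conduct of the follow-up do not change, but the stated BMI figure becomes less favourable.

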**c. Statistical Analysis.**

All analyses will allow appropriately for the clustering. We will use random effects models to account for correlation within polyclinic, as is recommended for cluster randomized trials. Results will be reported as mean differences. We will derive 95% confidence intervals and Wald tests of the null hypothesis of no association between intervention groups. Effect modification will be addressed by stratification and by formally testing for statistical interaction by introducing appropriate cross-product terms. We will initially examine results stratified by sex to ensure comparability, before we consider combining results for boys and girls.

It is well known that “per-protocol” analyses of randomized trials, in which participants are grouped according to the intervention they received, rather than that to which they were randomized, may be seriously biased. It is for this reason that the primary analyses for this study will be based on intention-to-treat. However, this approach may substantially underestimate the effect of the true exposure of interest (breastfeeding exclusivity and duration), since there was not complete contrast of breastfeeding status between the randomized groups: many intervention mothers did not exclusively breastfeed for 6 months, whereas some control mothers did. There is a substantial statistical literature showing that causal effects of interventions may be validly estimated from randomized trials, allowing appropriately for non-compliance with the intervention.^152-155^ Thus, in secondary analyses, we will apply instrumental variable methods to estimate the causal effect of the difference in breastfeeding exclusivity and duration achieved between the two randomized groups on our outcomes. In this approach, we will use randomization status as the ‘instrument’ that is independent of any confounders of the exposure-outcome relationship, and is related to the outcomes only via the exposure. We will thus validly estimate the unbiased effect of breastfeeding itself on cognition, vision, and lung function. Although these analyses will address the attenuation of the effect of breastfeeding that is inevitable in intention-to-treat analyses, they are unlikely to increase the power of the study, so sample size calculations are not affected.

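### Table 5 claims 80% power for a standardized difference of 0.1, but the stated effective sample gives about 70.5%, and its rows use three multipliers (0.10, 0.12 and 0.012 SD)

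*Protocol*

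**What the plan says.** Section 2.3.6 (Power) of the protocol starts from the number to be followed up, "we expect 14,000 participants in PROBIT IV", in 31 clusters. It asks for "80% power, 5% significance" and "used a realistic value (0.01) of the intra-cluster correlation coefficient (ICC"). From these it derives a design effect of 5.5 and an effective sample of 2,500, later split into 1,250 per arm.

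One rule is given for all continuous outcomes: the detectable difference is the SD times "the standardized difference (i.e. 0.1 given an effective sample size of 2,500^157"). The title of Table 5 repeats the operating characteristics: "differences detectable (alpha= 0.05, 80% Power"). Two of its rows read "Global cognitive score | 100 | 15 | 1.5 | 4.1" and "Systolic blood pressure (mmHg)^159^ | 99.9 | 9.6 | 1.15 | 3.11"; the last two figures in each are the intention-to-treat (ITT) difference and the breastfeeding effect, which is that difference divided by 0.37.

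Sidedness is not written in the power section. Section 2.3.5c describes the analysis: "We will derive 95% confidence intervals and Wald tests of the null hypothesis of no association between intervention groups".

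**The concern.** A standardized difference of 0.1 is not what an effective sample of 2,500 detects with 80% power in a two-sided 5% test. The rows of Table 5 also do not share one ratio of difference to SD, although the text gives a single rule.

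Section 2.3.6 uses this table to conclude that the sample is adequate, by setting the breastfeeding-effect column beside published differences. Where that column is too small, adequacy is overstated. A null result on cognition, lung function or vision would be read against a type II error of 20% when the plan's own inputs give about 30%. For BMI the printed figure suggests a sensitivity that the study does not have.

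**Working it through.** **The protocol's own steps**

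- Cluster size: 14,000/31 = 451.6. Design effect: 1 + 450.6 × 0.01 = 5.5. Effective sample: 14,000/5.5 = 2,545, which the protocol rounds to 2,500.
- Standard error of a standardized difference with 1,250 per arm: √(2/1250) = 0.04.
- Half-widths of the null confidence intervals, 1.96 × 0.04 × SD: cognition 1.18 (printed 1.2), FEV1 37.6 (40), FVC 45.1 (45), PEFR 62.7 (60). These reproduce to rounding, so the protocol itself works with SE 0.04 and the two-sided 1.96.

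**The multiplier**

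- 80% power, two-sided 5%: (1.960 + 0.842) × 0.04 = 0.112 SD. With 2,545 in place of 2,500 it is 0.111.
- Power at 0.10 SD: Φ(0.10/0.04 − 1.96) = Φ(0.54) = 70.5%; with 2,545 it is 71.3%.
- Power at 0.12 SD: Φ(3.0 − 1.96) = 85.1%.
- Effective total needed for 80% power at 0.10 SD: 4 × (2.802/0.10)² ≈ 3,140.

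The same section thus conflicts with itself: an interval of ±1.2 for cognition implies SE 0.6 and an 80% detectable difference of 2.80 × 0.6 = 1.68, while Table 5 prints 1.5.

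**Row by row** (effective N 2,500, two-sided)

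| Outcome | SD | Printed ITT difference | Ratio to SD | Power at printed difference | 80% difference (0.112 SD) | Divided by 0.37 | Printed breastfeeding effect |
|---|---|---|---|---|---|---|---|
| Cognition | 15 | 1.5 | 0.100 | 70.5% | 1.68 | 4.5 | 4.1 |
| FEV1 (ml) | 480 | 48 | 0.100 | 70.5% | 54 | 145 | 130 |
| FVC (ml) | 575 | 58 | 0.101 | 71.3% | 64 | 174 | 150 |
| PEFR (ml/s) | 800 | 80 | 0.100 | 70.5% | 90 | 242 | 200 |
| LogMAR | 0.2 | 0.02 | 0.100 | 70.5% | 0.022 | 0.061 | 0.05 |
| SBP (mmHg) | 9.6 | 1.15 | 0.120 | 85.0% | 1.08 | 2.9 | 3.11 |
| DBP (mmHg) | 6.8 | 0.82 | 0.121 | 85.4% | 0.76 | 2.1 | 2.22 |
| BMI (kg/m²) | 2.0 | 0.024 | 0.012 | 5 to 6% | 0.22 | 0.61 | 0.06 |

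For BMI, 0.012/0.04 = 0.3. Then Φ(0.3 − 1.96) = 4.8% in one tail, and Φ(−0.3 − 1.96) = 1.2% in the other gives 6.0% in total. A value of 0.24 would be 0.12 SD, the multiplier of the two blood pressure rows, which is why a decimal slip is the likely source. The slip carries through: 0.024/0.37 = 0.065, printed 0.06.

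**Dependence on the ICC, for systolic pressure**

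Table 4 gives an ICC of 0.12. The design effect is then 1 + 450.6 × 0.12 = 55.1, the effective sample 14,000/55.1 = 254, and the multiplier 2.802 × √(4/254) = 0.351. The detectable difference is 0.351 × 9.6 = 3.4 mmHg. The interval reported in section 1 for age 11.5 years (−1.1 to 3.1) points the same way: SE = 4.2/3.92 = 1.07, and 2.80 × 1.07 = 3.0 mmHg.

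**The case against.** **One-sided testing.** Because sidedness is not written, a one-sided 5% test could be meant; it gives 80.4% at 0.10 SD. This does not fit the planned 95% intervals and Wald tests of no association, or the null intervals built on 1.96. The 94% eczema power also reproduces two-sided (94.0%) rather than one-sided (96.9%), if the PROBIT I rates of 6.3% and 3.3% were its basis. That is an assumption; an exact halving of 6.3% gives about 96% two-sided. One-sided testing would also leave the blood pressure rows at about 91% and BMI at about 9%, so no single convention puts the whole table at 80%.

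**Rounding.** The 0.1 may be 0.112 shown to one decimal. But the rounded value was multiplied through: 1.5/0.37 = 4.05 gives the printed 4.1, and 0.02/0.37 = 0.054 gives the printed 0.05, whereas 0.0224/0.37 would print as 0.06.

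**Limited consequence.** This largely stands. The study tries to follow up everyone enrolled in PROBIT I, so sample size is not being chosen. Cognition moves from 4.1 to 4.5, still within the cited 2 to 5. The lung rows already exceed the cited differences as printed. The comparison with published figures changes for LogMAR (0.05 to 0.061, against 0.05) and BMI (0.06 to 0.61, against 0.28 to 0.57).

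**Stronger readings that the protocol does not support:**

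- That power is really 68%. This uses a t reference with 29 df (0.116 SD for 80% power). The protocol plans Wald tests from random effects models and fixes no degrees of freedom, so this is an optional refinement.
- That the blood pressure rows are simply conservative and systolic pressure can be detected at 1.08 mmHg. This holds only at an ICC of 0.01, against 0.12 in Table 4.
- That the main outcome is underpowered. Section 2.3.5b lists eight main cognitive scores and ranks none of them first.
- That 150 for FVC (58/0.37 = 157) and 200 for PEFR (80/0.37 = 216) are separate errors. They can be read as coarse rounding, and recomputation replaces them anyway.

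**Conclusion.** The point holds, at moderate severity. On the protocol's own inputs, 0.1 SD has about 70.5% power and 80% needs 0.112 SD. Table 5 applies three multipliers where the text states one, and six of eight rows miss 80%: five by about nine percentage points and BMI almost entirely. The two blood pressure rows exceed it, but only at the assumed ICC.

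This rests on a two-sided test (inferred, not stated), equal arms of 1,250 effective children, and an ICC of 0.01 for every outcome. The arithmetic error does not depend on whether that ICC is right, but the corrected values do. A reader might infer that the study needs more participants or is inadequate overall. The documents do not support that: the cohort is fixed, and most comparisons with published differences are unchanged.

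**What to change.** State that the test is two-sided. Replace 0.1 in section 2.3.6 with 0.112, and recompute every row of Table 5 with that multiplier and the 0.37 divisor, giving the values tabulated above. Correct the BMI row in the same pass.

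Relabelling the 0.10 rows as 70% power is not enough, because rows at about 70%, 85% and 5% would still share one table.

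Add a note that the recomputed values hold only at an ICC of 0.01. For systolic pressure, give the value at the Table 4 ICC of 0.12 (about 3.4 mmHg), at least beside the 1.08. If a small-sample t reference is intended, name it and use 0.116 SD throughout.

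After recomputing, revisit the adequacy sentence for LogMAR and BMI.

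Cost: one table and a few sentences. At an ICC of 0.01, five rows rise by 11 to 12% (for example 1.68/1.5 = 1.12), the blood pressure rows fall by 6 to 7% (1.08/1.15 = 0.94; 0.76/0.82 = 0.93), and BMI rises about ninefold (0.224/0.024 = 9.3). Recruitment and analysis are unchanged.
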